## Abstract

Isolated rapid eye movement sleep behavior disorder is a strong clinical marker of future alpha-synucleinopathy, but earlier stages of this risk pathway remain insufficiently characterized. Rapid eye movement sleep without atonia is the polysomnographic substrate of this disorder and may also be detected in individuals without clinical dream-enactment behavior. Whether isolated rapid eye movement sleep without atonia is a benign finding or an early risk state for future rapid eye movement sleep behavior disorder and neurodegeneration remains unknown. DREAMER is a multicenter, prospective, observational cohort protocol designed to identify adults without clinical rapid eye movement sleep behavior disorder who show isolated rapid eye movement sleep without atonia during full-night laboratory video-polysomnography. Four Italian sleep centers will use harmonized eligibility criteria, standardized clinical and sleep assessment, quantitative REM Atonia Index scoring, secure web-based data capture, and planned longitudinal follow-up. Adults aged 40 years or older undergoing video-polysomnography will be screened. Participants with prior rapid eye movement sleep behavior disorder or technically inadequate REM sleep/chin electromyographic data will be excluded. Isolated rapid eye movement sleep without atonia will be defined in participants without clinical rapid eye movement sleep behavior disorder using a REM Atonia Index threshold of <0.85. The target recruitment is more than 500 participants over 18 months, with an expected enriched subgroup of approximately 85 individuals with isolated rapid eye movement sleep without atonia. Ancillary neurophysiological assessments and blood sampling for future biomarker studies will be obtained when feasible. DREAMER is intended to create a harmonized, trial-ready cohort for evaluating isolated rapid eye movement sleep without atonia as a potential early risk marker for incident rapid eye movement sleep behavior disorder and subsequent neurodegenerative outcomes. The study is registered at ClinicalTrials.gov as DREAMER, ClinicalTrials.gov Identifier NCT06140511.

## 1. Introduction

REM sleep behavior disorder (RBD) is characterized by dream-enactment behavior associated with loss of physiological muscle atonia during REM sleep [1]. When RBD occurs in the absence of an established neurological disorder or other clearly causative condition, it is commonly regarded as an isolated form of RBD and has become one of the most powerful clinical markers of prodromal alpha-synucleinopathy. Longitudinal studies have shown that a large proportion of patients with isolated RBD eventually develop Parkinson disease, dementia with Lewy bodies, or multiple system atrophy, often after a prolonged interval [1–3].

The central diagnostic polysomnographic feature of RBD is REM sleep without atonia (RSWA). However, RSWA is not limited to clinically manifest RBD [4]. Quantitative PSG studies have shown that isolated RSWA/RWA can be detected in individuals without clinical RBD or dream-enactment behavior, with age, sex, medication exposure, psychiatric status, sleep-disordered breathing, and referral context influencing its frequency and interpretation [5–9]. This raises an important but unresolved question: does isolated RSWA represent a benign polysomnographic variant, a medication-related phenomenon, or an early risk state along the pathway toward RBD and synucleinopathy? Small longitudinal and retrospective sleep-clinic studies have suggested that isolated RSWA may be associated with subsequent RBD or neurodegenerative outcomes, whereas more recent registry-linked data emphasize that iRSWA is heterogeneous and not equivalent to iRBD [10–12]

This question has direct implications for clinical trial design. Neuroprotective and disease-modifying trials in alpha-synucleinopathies increasingly require identification of individuals at very early stages, ideally before overt motor or cognitive neurodegenerative syndromes emerge. Isolated RBD already provides a high-risk population, but it may not represent the earliest detectable stage. If isolated RSWA identifies at least a subgroup of individuals upstream of RBD, it could widen the prevention window and provide a biomarker-enriched population for future risk-stratified trials [4,10,11]. At present, however, isolated RSWA lacks standardized prospective cohort infrastructure, harmonized multicenter ascertainment, and longitudinal evidence sufficient to support its use as a trial-enrichment criterion.

The DREAMER study, Isolated REM sleep without Atonia as a risk factor for REM sleep behavior disorder, is designed to address this methodological gap. DREAMER is not an interventional clinical trial. Rather, it is a multicenter, prospective, registry-like cohort created to identify individuals with isolated RSWA among adults undergoing laboratory video-polysomnography (vPSG), harmonize their clinical and neurophysiological characterization, and establish a long-term follow-up platform to determine whether isolated RSWA predicts incident RBD and, eventually, alpha-synucleinopathy. The study is explicitly designed as trial-enabling infrastructure: it standardizes eligibility definitions, quantitative RSWA assessment, electronic data capture, biomarker collection, and risk-management procedures required for future preventive or disease-modifying studies.

This article describes the rationale, design, operational methodology, data-management framework, planned analyses, and risk-mitigation strategy of DREAMER, with emphasis on elements relevant to clinical trial readiness.

## 2. Materials and methods

### 2.1. Objectives

The primary objective of DREAMER is to establish a multicenter, harmonized, trial-ready cohort of adults without clinical RBD in whom isolated RSWA can be identified quantitatively by vPSG and followed longitudinally for the development of RBD.

The secondary objectives are:

To estimate the frequency of isolated RSWA in adults aged ≥40 years undergoing laboratory vPSG across participating sleep centers.To compare clinical, sleep, pharmacological, and neurophysiological characteristics between participants with and without isolated RSWA.To evaluate whether quantitative RSWA severity, measured by the REM Atonia Index (RAI), is associated with clinical and instrumental markers potentially relevant to prodromal synucleinopathy.To create a secure, quality-controlled electronic dataset suitable for future long-term phenoconversion analyses.To establish a biobank and multimodal biomarker framework that can support future mechanistic and prevention-oriented studies.

The long-term objective, beyond the 24-month cohort-construction period, is to determine whether baseline isolated RSWA is associated with higher risk of incident RBD and subsequent neurodegenerative outcomes compared with absence of RSWA.

### 2.2. Study design

DREAMER is a multicenter, prospective, observational cohort with registry-like data architecture. The study includes a 24-month phase dedicated to protocol harmonization, ethics approval, electronic case report form (eCRF) implementation, recruitment, baseline vPSG-based classification, and collection of ancillary biomarker data. Long-term follow-up is planned after completion of recruitment. The overall DREAMER workflow, from screening to longitudinal outcome ascertainment and trial-ready cohort construction, is shown in Fig 1, and the core design elements of DREAMER and their relevance to future trial readiness are summarized in Table 1.

**Table 1 pone.0350467.t001:** DREAMER design elements.

Design element	Operational implementation	Trial-readiness relevance
**Multicenter cohort**	Four Italian sleep centers recruit adults undergoing vPSG	Improves feasibility, generalizability, and recruitment scalability
**Harmonized eligibility**	Adults ≥40 years, no prior RBD, adequate REM sleep and chin EMG signal	Creates reproducible risk-enrichment criteria
**Quantitative RSWA**	Automated RAI; isolated RSWA defined as RAI < 0.85 without clinical RBD	Provides scalable biomarker-based classification
**Secure eCRF**	Web-based data capture with relational database and role-based access	Supports registry infrastructure and future trial operations
**Quality assurance**	SOPs, training, data dictionary, range checks, central review	Reduces cross-center variability
**Ancillary biomarkers**	TMS, VEMPs, BAEPs, and blood-based omics when feasible	Enables mechanistic stratification and future nested studies
**Long-term follow-up**	Incident RBD and neurodegenerative diagnoses	Supports validation of isolated RSWA as a prevention-trial enrichment marker

**Fig 1 pone.0350467.g001:**
[figure not shown]
DREAMER study workflow. Adults aged ≥40 years undergoing full-night laboratory video-polysomnography are screened for eligibility. After exclusion of participants with prior REM sleep behavior disorder or technically inadequate REM sleep/chin electromyography data, the REM Atonia Index is computed to classify participants with isolated REM sleep without atonia and comparator participants without isolated REM sleep without atonia. Baseline multimodal characterization, secure electronic case report form-based data capture, and longitudinal follow-up support the creation of a trial-ready platform for future prevention studies. RBD, REM sleep behavior disorder; REM, rapid eye movement; EMG, electromyography; RAI, REM Atonia Index; RSWA, REM sleep without atonia; PSG, polysomnography; TMS, transcranial magnetic stimulation; VEMPs, vestibular-evoked myogenic potentials; BAEPs, brainstem auditory evoked potentials; eCRF, electronic case report form.

The study has three operational phases:

**Phase 1: Harmonization and infrastructure development:** During the initial months, participating centers will agree on eligibility criteria, clinical variables, vPSG procedures, RAI computation, ancillary neurophysiological protocols, blood-sample collection procedures, data dictionary, and quality-control rules. A secure web-based eCRF will be implemented.

**Phase 2: Recruitment and baseline phenotyping:** Adults undergoing full-night laboratory vPSG will be screened. Participants without prior RBD and with technically adequate REM sleep recordings will be classified according to quantitative RAI values. Clinical, pharmacological, sleep, neurophysiological, and biobanking data will be collected according to the shared protocol.

**Phase 3: Long-term follow-up:** Participants with isolated RSWA and a comparator group without RSWA will be followed to identify incident RBD and neurodegenerative outcomes. The follow-up component is intended to continue beyond the initial funding period and to provide the evidentiary basis for future risk-stratified prevention trials.

The schedule of screening, baseline, ancillary, and follow-up assessments is shown in Table 2.

**Table 2 pone.0350467.t002:** Schedule of assessments.

Study phase	Procedure	All enrolled participants	Isolated RSWA subgroup
**Screening**	Eligibility review and informed consent	X	X
**Baseline**	Clinical and sleep history	X	X
**Baseline**	Medication and comorbidity assessment	X	X
**Baseline**	Full-night laboratory vPSG	X	X
**Baseline**	RAI computation	X	X
**Baseline**	RBD symptom/questionnaire assessment	X	X
**Baseline**	TMS	As feasible	Priority
**Baseline**	VEMPs/startle response	As feasible	Priority
**Baseline**	BAEPs	As feasible	Priority
**Baseline**	Blood sampling for biobank	As feasible	Priority
**Follow-up**	Annual assessment for dream-enactment behavior	Planned	X
**Follow-up**	Repeat vPSG	If clinically indicated or protocol-defined	X
**Follow-up**	Neurodegenerative outcome ascertainment	Planned	X

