### 2.4. Study population, inclusion and exclusion criteria

Participants will be recruited among adults undergoing full-night laboratory vPSG for clinical indications at participating centers. The target population is intentionally pragmatic: it reflects real-world sleep-center populations in which incidental RSWA may be detected and future risk stratification may become clinically relevant.

Participants must meet all of the following criteria:

Age ≥ 40 years at baseline.Ability to understand study procedures and provide written informed consent.Undergoing full-night laboratory vPSG with video recording.Availability of chin electromyographic signal of sufficient technical quality for RAI computation.At least 5 minutes of artifact-free REM sleep.No prior clinical diagnosis of RBD.

Collateral history from a bed partner, roommate, or other reliable informant will be collected whenever available to improve ascertainment of dream-enactment behavior. This is particularly important because the distinction between iRSWA and iRBD may be influenced by the availability of an observer or co-sleeper, potentially leading to under-recognition of dream-enactment behavior [12].

Participants will be excluded if any of the following are present:

Prior diagnosis of RBD.Severe neurological, psychiatric, cognitive, or general medical condition that prevents valid participation or understanding of study procedures.vPSG recordings with major artifacts affecting the chin EMG signal during REM sleep.Less than 5 minutes of artifact-free REM sleep.Withdrawal of consent.

The protocol will record medications known to influence REM sleep muscle tone, particularly antidepressants, as well as comorbid sleep disorders and neurological conditions. These factors will not automatically exclude participation unless specified by the final protocol or judged to preclude valid classification, but they will be incorporated into sensitivity analyses.

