### 2.8. Follow-up procedures and phenoconversion ascertainment

Participants classified as having isolated RSWA and a comparator group without isolated RSWA will be invited to participate in longitudinal follow-up. Follow-up will be performed at least annually by in-person visit, telephone interview, video consultation, or review of clinical records, according to participant availability and local center procedures. The follow-up strategy is designed to detect two clinically relevant forms of phenoconversion: conversion to clinically manifest RBD and conversion to a neurodegenerative disorder within the alpha-synucleinopathy spectrum, in line with longitudinal evidence from isolated RBD cohorts and biomarker-based models of conversion risk [2,3].

At each follow-up contact, participants will be asked about the occurrence of new dream-enactment behavior, vocalizations or complex motor behaviors during sleep, sleep-related injuries, falls from bed, violent or disruptive sleep behaviors, and changes in sleep quality. Whenever possible, information will also be obtained from a bed partner, caregiver, roommate, or other reliable informant. Follow-up assessments will also record changes in medication exposure, especially antidepressants, benzodiazepines, melatonin, dopaminergic medications, antipsychotics, and other drugs potentially influencing REM sleep muscle tone or parasomnia expression. New diagnoses of sleep disorders, neurological disorders, psychiatric disorders, and relevant systemic illnesses will be recorded.

Incident RBD will be suspected when new recurrent dream-enactment behavior or other clinically relevant REM sleep-related motor behaviors are reported by the participant or an informant. In these cases, participants will be invited to undergo repeat full-night laboratory video-polysomnography, including chin electromyography and video documentation, whenever feasible. Incident RBD will be defined by the emergence of clinical dream-enactment behavior together with polysomnographic evidence of RSWA, according to accepted diagnostic criteria [1,22]. For each suspected or confirmed case, the date of first reported symptoms, date of clinical recognition, and date of polysomnographic confirmation will be recorded separately.

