Phenoconversion to neurodegenerative disease will be assessed through annual clinical history, neurological review, and documentation of any new diagnosis of Parkinson disease, dementia with Lewy bodies, multiple system atrophy, or other relevant neurodegenerative disorders, using established diagnostic frameworks where applicable [23–25]. Follow-up data collection will include symptoms or signs suggestive of parkinsonism, cognitive decline, visual hallucinations, fluctuating cognition, autonomic dysfunction, gait impairment, olfactory impairment, and other non-motor manifestations potentially relevant to prodromal synucleinopathy, consistent with research criteria and updates for prodromal Parkinson disease [26,27]. This approach is also supported by longitudinal application of prodromal Parkinson disease criteria in RBD cohorts [28].

When clinically indicated, participants will be referred for neurological evaluation and additional investigations according to local clinical practice, including neuropsychological testing, autonomic assessment, brain imaging, dopamine transporter imaging, or other biomarker investigations. These tests are not mandated by the protocol but will be recorded when available.

All suspected phenoconversion events will be reviewed by the recruiting center and, when necessary, discussed centrally by the study investigators. Outcome adjudication will use predefined criteria and will distinguish between no conversion, possible RBD, confirmed RBD, possible neurodegenerative phenoconversion, and confirmed neurodegenerative diagnosis. For longitudinal analyses, the event date will be defined as the earliest reliable date of symptom onset when available; otherwise, the date of clinical diagnosis or polysomnographic confirmation will be used. Participants who cannot be contacted will be classified as lost to follow-up after repeated contact attempts, and the date of last available assessment will be recorded.

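### Table 2 and Section 2.8 conflict on who gets a repeat vPSG; if Table 2 governs, RBD would be confirmed preferentially in the isolated-RSWA group and the Cox hazard ratio would tend to be biased upward

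*Protocol article*

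**What the plan says.** **Table 2 (Section 2.2).** The table has two columns, one for all enrolled participants and one for the isolated-RSWA subgroup. Repeat vPSG during follow-up is marked X for the subgroup and "If clinically indicated or protocol-defined" for all enrolled. The row "Annual assessment for dream-enactment behavior" is marked X for the subgroup and as planned for all enrolled. Comparators have no column of their own.

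**Section 2.8.** The text does not separate the groups: "Participants classified as having isolated RSWA and a comparator group without isolated RSWA will be invited to participate in longitudinal follow-up". On frequency it says: "Follow-up will be performed at least annually by in-person visit, telephone interview, video consultation, or review of clinical records". Repeat vPSG depends on newly reported behavior: "In these cases, participants will be invited to undergo repeat full-night laboratory video-polysomnography, including chin electromyography and video documentation, whenever feasible".

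**Outcome and adjudication.** Sections 2.7 and 2.8 define incident RBD as dream enactment plus RSWA on vPSG. Section 2.8 grades events as possible or confirmed and dates them from symptom onset where that is reliably known. On review it says: "All suspected phenoconversion events will be reviewed by the recruiting center and, when necessary, discussed centrally by the study investigators". It does not say that reviewers are masked to baseline RAI or group.

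**Analysis.** Section 2.11 plans Kaplan-Meier curves and a Cox model of isolated RSWA against incident RBD. Its sensitivity analyses cover antidepressants, REM duration, sleep apnea and RAI thresholds.

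**The concern.** The long-term question is whether isolated RSWA carries a higher risk of RBD. That comparison is fair only if an event is equally likely to be found and confirmed in both groups. Here the confirming test is part of the case definition, and Table 2 ties that test to the exposure.

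Take two participants who report the same new behavior. Under Table 2, the one with isolated RSWA has a repeat vPSG in the schedule, which can turn possible RBD into confirmed RBD. The other has one only if a condition is met, and may stay at possible. Some of the observed difference would then reflect testing rather than disease.

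Nothing stated offsets this. The masking in Section 2.5 concerns the automated RAI, whose output may not be adjusted by hand anyway. The Discussion admits that repeat vPSG may vary by center and over time, but does not mention variation by exposure group. Section 2.9 intends the relative-risk estimates for planning prevention trials, so an inflated ratio would carry over into those designs.

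**Working it through.** **1. The two places side by side**

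| Item | Table 2, isolated RSWA | Table 2, all enrolled | Section 2.8, both followed groups |
|---|---|---|---|
| Annual contact | X | Planned | At least annual |
| Repeat vPSG | X | Conditional | After reported symptoms, where feasible |

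The annual-contact row can be squared with Section 2.8. The repeat-vPSG row cannot: a site cannot tell whether vPSG in the isolated-RSWA group is scheduled or triggered by symptoms.

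**2. The plan's own figures**

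The document gives no hazard ratio, event count, RBD incidence or detection probability, so there is no figure on this point to reproduce. Section 2.9 supplies only the scale: about 85 participants with isolated RSWA from a target above 500, which leaves 500 − 85 = 415 others at the minimum.

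**3. Size of the effect if Table 2 is followed**

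Assumed inputs, none from the document:
- true 5-year comparator risk R = 0.05 (range 0.02 to 0.10);
- probability that a true case is confirmed: s1 = 0.90 in isolated RSWA, and s0 = 0.75, 0.60 or 0.45 in comparators.

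Formulas:
- true risk in isolated RSWA: R1 = 1 − (1 − R)^HR
- confirmed risks: d1 = R1 × s1 and d0 = R × s0
- apparent hazard ratio: ln(1 − d1) / ln(1 − d0)

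True hazard ratio 1, R = 0.05, so d1 = 0.05 × 0.90 = 0.045:
- s0 = 0.75: d0 = 0.0375; ln(0.955)/ln(0.9625) = 1.20
- s0 = 0.60: d0 = 0.0300; ln(0.955)/ln(0.970) = 1.51
- s0 = 0.45: d0 = 0.0225; ln(0.955)/ln(0.9775) = 2.02

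For R from 0.02 to 0.10 these become 1.20–1.21, 1.50–1.52 and 2.01–2.05, so the baseline risk hardly matters. The apparent ratio is close to the true ratio times s1/s0.

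True hazard ratio 2, R = 0.05: R1 = 1 − 0.95² = 0.0975 and d1 = 0.08775. The apparent ratios are 2.40, 3.02 and 4.04.

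**4. Chance of a falsely significant upward result**

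Take true hazard ratio 1, R = 0.05 and 85 against 415 participants. With E expected confirmed events in total, the approximate probability at two-sided 0.05 is Φ(√(E × 0.17 × 0.83) × ln(apparent HR) − 1.96), where 0.17 = 85/500.

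| s0 | Confirmed events, isolated RSWA / others | Probability |
|---|---|---|
| 0.90 | 3.8 / 18.7 | 2.5% |
| 0.75 | 3.8 / 15.6 | 4.9% |
| 0.60 | 3.8 / 12.4 | 9.1% |
| 0.45 | 3.8 / 9.3 | 15.9% |

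With so few events this approximation is rough. It also treats all 415 others as comparators, although Sections 2.9 and 2.12 allow for a selected, matched group.

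**5. Check with equal confirmation**

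Setting s1 = s0 = 0.90 returns 1.00 for a true ratio of 1, and 1.99 to 2.00 for a true ratio of 2 over the same range of R.

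**The case against.** The strongest reply is that the bias exists only if Table 2 governs. Under Section 2.8 both groups have the same questions, contact frequency and vPSG trigger, and the scheduled difference disappears. In addition, the second column of Table 2 is all enrolled participants, not comparators, and its words about protocol-defined testing could cover scheduled vPSG for comparators. This stands, and it makes the bias conditional. It does not settle which rule sites will follow.

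It is also fair that RBD requires dream enactment as well as vPSG evidence. That limits the effect. Dating events from symptom onset protects their timing, but not their confirmation.

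A reader might infer more than the document supports:
- **That comparators get weaker annual assessment.** Planned does not mean omitted, and Section 2.8 commits to at least annual follow-up in both groups.
- **That events can arise only in the isolated-RSWA group.** Comparators with reported symptoms can also be confirmed. Whether behavior seen only on video would count depends on cited criteria that are not shown.
- **That change in RAI is distorted in the same direction.** If comparators are rescanned mainly when symptomatic, those rescanned may be the ones who have worsened, which could narrow or reverse a group difference.
- **That reviewers certainly know the baseline group.** Section 2.12 places classification before follow-up and Section 2.6 selects participants for ancillary tests by RSWA status, so knowledge is likely. The document does not say who sees the result.
- **That informant availability must enter the model.** Section 2.4 does say that "the distinction between iRSWA and iRBD may be influenced by the availability of an observer or co-sleeper", but availability at each contact is a post-baseline variable, and adjusting for it is a modelling preference.

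Finally, the primary objective is to build the cohort, and Section 2.9 calls the relative-risk estimates preliminary. That lowers the stakes but does not remove the conflict.

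**Conclusion.** The concern holds in a conditional form. Table 2 and Section 2.8 disagree on whether repeat vPSG in the isolated-RSWA group is scheduled or symptom-triggered. Because vPSG evidence is part of the outcome definition, following Table 2 would confirm RBD preferentially in that group and would tend to push the Cox hazard ratio upward. No stated masking, case definition or sensitivity analysis counters this.

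The size is illustrative. With no true difference and assumed confirmation of 0.90 against 0.75 to 0.45, the apparent hazard ratio is about 1.2 to 2.0. The lower end, a modest distortion, is as compatible with the document as the upper end. It cannot be said from the document that the hazard ratio will be biased, or by how much.

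**What to change.** Make these changes before follow-up begins; Section 2.12 places its start after recruitment, which is expected to end by 30 June 2026.

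1. Reconcile Table 2 with Section 2.8 on repeat vPSG, stating the rule separately for the isolated-RSWA and comparator groups.
2. In the Kaplan-Meier and Cox analyses, count as events only RBD reached through the symptom-report pathway common to both groups. Report events found only on a scheduled vPSG separately. This requires recording why each repeat vPSG was done.
3. Add a sensitivity analysis that counts possible plus confirmed RBD, so that the result depends less on who was retested.
4. Remove baseline RAI and group from the file used for adjudication.

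A sensitivity analysis by informant availability at baseline is optional.

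**Cost.** The first three items are a table edit, an event definition and one further analysis. Masked review takes some organization, because the four recruiting centers make the first assessment themselves. The statistical price is small: events found only on a scheduled vPSG leave the between-group comparison. Vigilance is cheap now, whereas a vPSG never done in a comparator cannot be recovered by later analysis.
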